|                                                                                                                                                      |                                                                                                                                                                                |                                                                                                                                                                                                                                                                                                                                                                                                                   |
|------------------------------------------------------------------------------------------------------------------------------------------------------|--------------------------------------------------------------------------------------------------------------------------------------------------------------------------------|-------------------------------------------------------------------------------------------------------------------------------------------------------------------------------------------------------------------------------------------------------------------------------------------------------------------------------------------------------------------------------------------------------------------|
|                                                                                                                                                      |                                                                                                                                                                                | 
CFH Docmail data) as a % of all women sent 15-month mailout pre-notification letter
 
Vs
 
Number of women who attend for conventional screening in months 12-14 as a % of all women who reach the 12-month anniversary of their last test due date without being screened (NHAIS data)
                                                                                                          |
| To ensure robust pathways are established for accurately identifying non-attenders for mail-out and opportunistic offer                              | Proportion of women accurately identified for (i) mail-out and (ii) opportunistic offer                                                                                        | Number of women who are correctly (i.e. eligible) and incorrectly (i.e. ineligible) identified in NHAIS as eligible for 15m mailout (NHAIS data) and (ii) ≥6m overdue cervical screening in GP primary care (GP and NHAIS data) as a % of all women identified for (i) 15m mailout and (ii) opportunistic offer, respectively (GP and NHAIS data)                                                                 |
| To assess the demographic characteristics, cervical screening status and previous barriers to screening uptake of women who respond to self-sampling | Uptake of cervical screening by age bands, ethnic group, LSOA, cervical screening status (never screened, overdue, up-to-date) and reported reason for previous non-attendance | Number of women who return a self-sample in (i) 10 year age bands (NHAIS data), (ii) British Census ethnicity categories (GP record and survey data), (iii) cervical screening status (NHAIS data) and (iv) reason for previous non-attendance (survey data) as a % of all women who return a self-sample                                                                                                         |
| To estimate the impact of offering self-sampling on long-term coverage (Long-term follow-up: future analysis)                                        | Coverage at 13 months after trial recruitment ends                                                                                                                             | 
“Coverage” calculated at 13 months after last woman was sent/given a kit (NHAIS data) calculated separately for 3 different groups of women:
 
 
1) 0-14m (women overdue but who were not sent a kit),
 
2) 15m+ (women overdue who were sent a kit),
 
3) 16-26m (women overdue but not sent a kit because past 15m timepoint at trial start)
 
 |
| To estimate the (long term) NPV & PPV of self-sampling (Long-term follow-up: future analysis)                                                        | CIN2+ rates at 3y and 6y after trial end in women who return a self-sample by (i) HPV negative and (ii) HPV positive                                                           | Number of women with histologically confirmed CIN2+ (i.e. CIN2, CIN3 or invasive cervical cancer) in women who return a self-sample as a % of all women return a self-sample separately for (i) HPV negative and (ii) HPV positive (aggregate anonymous data from Cyres and the National Cancer Registration and Analysis Service)                                                                                |

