| To estimate the uptake and increase in coverage associated with offering self-sampling              | 
1. Uptake of kits at 30 days, 90 days and at the end of the trial*
 
2. Change in coverage at participating GP practices (when additionally counting a negative HPV test on a self-sample as having been screened) from the start vs the end of the trial.
 
3. Change in the proportion eligible appropriately screened.
 | 
1. Uptake: number of women screened by self-sample (at 30 days and 90 days from date kit mailed out (from print company) or given out in GP practice (GP records), and total) (from NHAIS and central laboratory) as a % of all women sent kit or opportunistically offered kit (from NHAIS for 15m and from GP record data for opportunistic)
 
2. Coverage: Age-appropriate coverage (as determined by the number of women who have either been screened by cytology or HPV negative on a primary HPV test or self-sample in the past 3.5y if aged 25-49 or 5.5y if aged 50-64y as a % of all those eligible for cervical screening) at participating GP practices. The endpoint is the change in coverage from the (practice-specific) beginning to the (practice-specific) end of the trial (all NHAIS data).
 
3. Eligible women (on the first of each month): women not ceased from screening aged 25-49 who have not been screened within the last 2.9 years or aged 50-64 and not screened within the last 4.9 years.
Appropriately screened: number of eligible women screened within the month. Data will be collected separately for "conventional screen", "return of mailout kit" and "return of opportunistic kit". The proportion eligible screened (by any approach) will be recorded each month during the trial and for the four months before the trial start. The average for the before and after period will be compared.
 |

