| To assess the impact of self-sampling on inequalities                     | Uptake of self-sampling kits according to (i) ethnic group and (ii) Lower Layer Super Output Area (LSOA) overall and by mode of kit offer    | Compare distribution of (i) ethnicity (British Census categories from GP records and self-report on survey) and (ii) LSOA (from NHAIS) for women who have a self-sample result (NHAIS data linked with GP record data) overall, and by mode of kit offer (mailout vs opportunistic offer)
Vs 
 
women who have a standard screening test (NHAIS data linked with GP record data) over the trial period and
 
women who are <math>\geq 6m</math> overdue (mailout or eligible for opportunistic offer) but not screened by any method during trial (i.e. non-responders).
 
 |

|                                                                                                                                                                                               |                                                                                                                                                             |                                                                                                                                                                                                                                                                                                                                                                                                                                                                                                                                  |

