### 7.2.2 Opportunistic offering

Women targeted for opportunistic offering will be identified using the GP patient record software system (date of last recorded cervical screening test). Although cervical screening records in GP records are sometimes not up to date, this method of identifying the relevant cohort for opportunistic offering is currently the only viable option (GP patient records are not linked to the national screening database (NHAIS)).

An alert will be set up on the electronic patient record (EPR) software to automatically flag potentially eligible women when their record is opened. Specifically, EPR systems will be programmed to flag women aged 25.5-64 years who are at least 6 months overdue cervical screening (i.e. no cervical screening test (cytology, HPV primary or self-sample) recorded in the past 3.5 years (if aged 25-49) or 5.5 years (if aged 50-64) and no codes for hysterectomy or amputation of cervix). The alert will be switched on at the practice start date.

Doctors, nurses and healthcare assistants (HCA)/assistant practitioners (AP) will be asked to offer self-sampling kits to women who have been flagged when they consult for any reason. In practice, this will be on a case-by-case basis at the discretion of the healthcare professional consulted. The trial invitation (kit offer) will comprise a brief conversation (~2 minutes) at the end of the consultation. Healthcare professionals will be asked to confirm the women's eligibility before handing them a self-sampling kit, which includes the patient information booklet.

A study template will be set up in the GP electronic patient record system. When women are offered kits, the consulting health professional will use the template to record:

- 1) Whether or not the trial kit was accepted.

- 2) If accepted: trial kit ID number
- 3) If declined:
  - a) Reason for declining (if logistics allow)
  - b) Consent or dissent to share anonymous data from their GP records and the national cervical screening database

If the woman accepts a kit, the consulting health professional will:

- Print out a lab request/consent form with the woman's details mail-merged using the EPR system to be returned with the sample
- Write the kit ID number on the lab request/consent form
- Write three of the NHS CSP acceptable identifiers on the tube label. Preferably these will comprise the woman's name, date of birth and postcode.

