## 9 STATISTICAL CONSIDERATIONS

### 9.1 Sample size considerations

This is a feasibility trial of the implementation of a new self-sampling pathway that is not designed to detect a difference between two arms. Rather, to estimate the increase in coverage associated with offering self-sampling to nonattenders, therefore, formal power calculations are not appropriate. In

addition, the trial aims to recruit as many women as possible that the budget will allow. Our budget allows for a return of approximately 10,000 samples and issuing of circa 31,000 kits.

According to the NHAIS 2017/18 data available online from the National General Practice Profiles (<https://fingertips.phe.org.uk/profile/general-practice>), across the five CCGs included in our trial there are 212 GP practices and 190,579 women who are  $\geq 6$  months overdue for cervical screening. Assuming 50% (106/212) of GP practices agree to take part, there would be approximately 95,000 ( $0.50 \times 190,579$ ) eligible women (i.e. women aged 25-64 eligible for cervical screening who are overdue by at least 6 months).

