### 9.1.1 Direct Mail-out

Assuming 106 GP practices recruit women for an average of 9 months (GP practices will recruit for a minimum of 6 months and a maximum of 12 months given that study set-up at each practice will be staggered over a 6 month period) and 20 women reach the 15 month anniversary at each practice each month, approximately 19,000 women will be sent kits during the trial. Table 2 below provides the expected 95% confidence intervals for various uptake levels over an average of 9 months recruitment period. We have estimated that 15% of women who receive a kit via direct mail-out will return a self-sample (i.e. ~2,800 women will return a self-sample over an average of 9m).

**Table 2 Expected 95% confidence intervals for different proportions of women who return a self-sample based on 106 GP practices over a 9-month average recruitment period**

| Uptake among those offered kits | 95%CI     |
|---------------------------------|-----------|
| 10%                             | 9.6-10.4  |
| 15%                             | 14.5-15.5 |
| 20%                             | 19.4-20.6 |
| 30%                             | 29.3-30.7 |

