### 9.1.2 Opportunistic offering of self-sampling

With an estimated 106 GP practices participating, there would be some 95,000 ( $190,579 \times (106/212)$ ) women eligible for opportunistic offering of kits. Based on our previous studies(16, 37)) we estimate that ~60% (57,000) will consult their GP practice over 9-12 months, some 17,100 (30%) will be offered a self-sampling kit and of those offered, ~12,000 (70%) will accept. We estimate that a total of ~8,500 would return a self-sample for HPV testing (50% of those offered i.e.  $17,000 \times 0.5$ ). Therefore, the proportion of women  $\geq 6m$  overdue cervical screening who will return a sample when opportunistically offered a kit (i.e.  $\approx 8,500/17,000$ ) could be estimated with a 95% confidence interval of width  $\pm 1.0\%$ .

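### The inequalities measure counts overdue women who were never sent or offered a kit as non-responders, so its comparator mixes inequality of offer with inequality of response

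*Protocol*

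**What the plan says.** In the table of Protocol section 3.2, the endpoint for the inequalities objective is "Uptake of self-sampling kits according to (i) ethnic group and (ii) Lower Layer Super Output Area (LSOA) overall and by mode of kit offer". The measure compares the ethnic and LSOA distribution of women who have a self-sample result with two groups. One is women who had a standard screening test over the trial period. The other is women at least six months "overdue (mailout or eligible for opportunistic offer) but not screened by any method during trial (i.e. non-responders".

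Elsewhere the protocol ties uptake to an actual offer. The primary uptake row of the same table counts returns "as a % of all women sent kit or opportunistically offered kit". The row on uptake by mode uses women sent a kit directly, or women with a Read code for a kit offered.

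Being eligible for an opportunistic offer is much wider than receiving one. Section 9.1.2 treats all overdue women at participating practices as eligible and expects that about 60% "will consult their GP practice over 9-12 months, some 17,100 (30%) will be offered a self-sampling kit". Section 7.2.2 says of the offer that "this will be on a case-by-case basis at the discretion of the healthcare professional consulted". Under section 6.1, mail-out reaches only the sub-group who come to the 15-month anniversary.

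**The concern.** Read as written, a woman who never consulted, or who consulted and was not offered a kit, and who did not reach 15 months during the trial, is classed as a non-responder. She had nothing to respond to. She also has no mode of offer, so she has no place in a comparison by mode.

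If one ethnic group consults less often, or is offered kits less often, it will look less willing to self-sample on this measure even when its response to an offer is the same as everyone else's. Section 17 says the findings will be used to propose policy. A gap in offers and a gap in response call for different action. In addition, section 14.2 justifies access to the records of non-consenting women partly by the wish to profile those who do not respond to the offer, and this comparator does not isolate them.

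**Working it through.** **Inputs (Protocol)**
- Overdue women at participating practices: "there would be approximately 95,000" (section 9.1)
- Mail-out: "approximately 19,000 women will be sent kits during the trial" (section 9.1.1)
- Mail-out returns: about "2,800 women will return a self-sample over an average of 9m" (section 9.1.1)
- Opportunistic: 57,000 consult, 17,100 offered, about 12,000 accept, about 8,500 return (section 9.1.2)

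**Reproducing the plan's figures**
- 190,579 × 106/212 = 95,290
- 106 × 20 × 9 = 19,080 mailed; × 0.15 = 2,862 returned
- 95,290 × 0.60 = 57,174 consult; × 0.30 = 17,152 offered; × 0.70 = 12,006 accept; 17,152 × 0.50 = 8,576 returned

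All agree with the stated rounded values, which are used below.

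**Share of the comparator never sent or offered a kit**
- Never sent or offered: 95,000 − 19,000 − 17,100 = 58,900
- Comparator as written: 95,000 − 8,500 − 2,800 = 83,700
- Sent or offered, no return: 83,700 − 58,900 = 24,800
- Share: 58,900/83,700 = 70.4%

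This assumes that the two routes do not overlap, that mailed women are among the 95,000, and that conventional screening falls equally on reached and unreached women.

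**Varying those assumptions**

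| Assumption | Share |
|---|---|
| Routes overlap independently: 95,000 × (76,000/95,000) × (77,900/95,000) = 62,320; /83,700 | 74.5% |
| Mailed women additional to the 95,000: 77,900/102,700 | 75.9% |
| All opportunistic offers go to mailed women: 76,000/83,700 | 90.8% |
| Conventional screening removes 10% or 40% of never-offered women only: 53,010/77,810; 35,340/60,140 | 68.1%; 58.8% |
| Conventional screening removes 10% or 40% of sent or offered women only: 58,900/81,220; 58,900/73,780 | 72.5%; 79.8% |

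The 10% and 40% are assumed, since the documents give no conventional-screening rate.

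For the opportunistic route alone, the share of eligible non-returners never offered a kit is (95,000 − 17,100)/(95,000 − 8,500) = 77,900/86,500 = 90.1%.

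**How the mixing works (assumed inputs)**

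Take two groups of equal size, with 70% and 50% consulting. In both, 30% of those consulting are offered a kit and 50% of those offered return it. Ignore mail-out and conventional screening.
- Returners as a fraction of each group: 0.70 × 0.30 × 0.50 = 0.105 and 0.50 × 0.30 × 0.50 = 0.075
- Odds ratio with the section 3.2 comparator: (0.105/0.075)/(0.895/0.925) = 1.45
- Odds ratio among women offered a kit: (0.105/0.075)/(0.105/0.075) = 1.00

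The whole of the 1.45 comes from consulting, and none from response.

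**The case against.** A reader might infer that the trial could not tell at all whether a gap by ethnicity or deprivation arises at the offer or at the response. The protocol does not support that. Section 9.2.2 plans mixed-effect models of uptake by pathway, ethnic group, LSOA and age. It does not restate the denominator, but sections 3.2 and 9.2.1 define uptake on women sent, offered or given a kit. An exploratory row in section 3.2 also covers acceptance and refusal among women offered kits. A comparison conditional on offer is therefore already planned.

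It can also be said that the objective is the impact on inequalities, and that setting the women reached against everyone left unscreened is a fair measure of population reach. For that purpose unequal consulting or offering is part of the programme's effect and should not be removed. This stands: the group is legitimate under the right name. What remains is that the protocol calls it non-responders and attaches it to an uptake endpoint.

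Finally, splitting a descriptive comparator could be left to the statistical analysis plan, to which section 9.2 defers detail. That would hold if the protocol were silent, but here it fixes the definition, and the definition conflicts with its own uptake rows.

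**Conclusion.** The point holds as a fault in one stated definition. On the planning figures about 70% of the women labelled non-responders would never have been sent or offered a kit, and they are a majority in every scenario tried (about 59% to 91%). The 70% is derived here and is not stated in the protocol. It treats the 95,000 as a fixed cohort, although it is a snapshot, and it rests on the assumptions set out in the working.

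The 70% should not be read as the share who never held a kit. Women who declined an offer did not hold one either, and counting them gives (95,000 − 19,000 − 12,000)/83,700 = 64,000/83,700 = 76.5%.

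The consequence is limited. The inequalities measure and the section 9.2.2 models would give two results for uptake by ethnic group and LSOA on different denominators, and these can disagree. The measure should be corrected, but it does not leave the question unanswerable.

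**What to change.** Reword the measure in section 3.2. Keep the condition of not being screened by any method and split the comparator:

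- **(a) Non-responders:** women sent a mail-out kit, or with a code for a kit offered, who stayed unscreened. Compare these with returners within mode, with a stated rule for women reached by both routes.
- **(b) Never sent or offered a kit:** overdue women with neither a mail-out nor an offer code who stayed unscreened.

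Report (a) and (b) together as unscreened overdue women to show population reach. Leave conventionally screened women in their existing separate group. Defining non-responders only by the absence of a returned self-sample would place women who received a kit and then had a conventional test in both comparators. State in section 9.2.2 that its uptake models use women sent or offered a kit, so that the two sections agree.

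No new data are needed. Date identified for mail-out (section 10.4.1), kits offered, accepted and declined (section 10.4.4) and kit dispatch dates (section 10.4.5) are all planned. The costs are a smaller response comparator, about 24,800 rather than 83,700 women before removing those screened conventionally, and reliance on clinician-entered offer codes for the opportunistic route. An uncoded offer would move a true non-responder into group (b).

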|-----------------------------------------------------------------------------------------------------------------------------------------------------------------------------------------------|-------------------------------------------------------------------------------------------------------------------------------------------------------------|----------------------------------------------------------------------------------------------------------------------------------------------------------------------------------------------------------------------------------------------------------------------------------------------------------------------------------------------------------------------------------------------------------------------------------------------------------------------------------------------------------------------------------|
| To estimate the cost effectiveness of this intervention                                                                                                                                       | Cost per woman screened or per case of CIN2+ detected                                                                                                       | Cost of self-sampling kit * total number of kits sent or offered (NHAIS & GP records) as a % of number of women with histologically confirmed CIN2+ in women who return a self-sample (Cyres data)                                                                                                                                                                                                                                                                                                                               |

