| To examine in more detail the opportunistic offer of self-sampling in GP primary care (if data allow)                                                                                                                                                                              | 
Response rates of eligible women offered kits in GP primary care
 
Reasons for declining kits
 
Kit offer and response to offer by health care professional type
 | 
The number of women who (i) accept a kit or (ii) decline a kit as a % of total number of eligible women offered kits opportunistically in GP primary care (GP record data)
 
Aggregated data on the main reasons for declining kits (GP records): number of women with each key reason provided as a % of all women recorded as declining kits (GP record data)
 
Number of kits (i) offered and (ii) accepted by health care professional type as a % of all kits offered (GP record data)
 |
| To assess any potential “nudge” effect towards the uptake of conventional screening associated with offering self-sampling                                                                                                                                                         | Uptake of conventional screening within 3 months of offer of self-sampling                                                                                                        | 
At participating GP practices:
 
Number of women who attend for conventional screening (and do not return a self-sample) within 3 months of the date of 15-month mailout pre-notification letter is sent (NHAIS &
                                                                                                                                                                                                                                                                            |

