### 9.1.3 Questionnaire-based sub-study

As the trial is designed to be descriptive, a formal power calculation is not possible. A previous study in Westminster, London(18) had a survey response rate of 97% among the 6% of women who completed a self-sample kit, and just under 1% for those who did not send back a kit. We therefore expect a very low response rate in women who do not return the kit, making statistical comparisons between completers and non-completers inappropriate. However, we plan to explore demographic patterns of PAPM stage, previous barriers and confidence in completing the kit (e.g. by ethnicity and level of deprivation) within the completer and (to a lesser extent) the non-completer groups, and to do this, we anticipate needing a relatively large sample.

We have allowed for a high response rate (90% for kit completers; 10% for non-completers) to avoid under-funding. This would yield a sample of ~5,500 kit completers and ~2,500 non-completers but we anticipate the actual sample size is likely to be somewhat lower.

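### The cost-effectiveness formula in Protocol section 3.2 charges declined offers, counts only kit cost, is stated as a percentage, and omits cost per woman screened

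*Protocol*

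**What the plan says.** The table in Protocol section 3.2 has a secondary objective on cost effectiveness. Its endpoint is "Cost per woman screened or per case of CIN2+ detected". The measure beside it is "Cost of self-sampling kit * total number of kits sent or offered (NHAIS & GP records) as a % of number of women" with confirmed CIN2+ who returned a self-sample. No second measure is given.

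The planning figures are in section 9.1. For the mail-out, "approximately 19,000 women will be sent kits during the trial". For the opportunistic pathway, "some 17,100 (30%) will be offered a self-sampling kit and of those offered, ~12,000 (70%) will accept". The Trial Summary adds 19,000 and 12,000 to reach 31,000 women receiving kits. Section 9.1 budgets for about 10,000 returned samples and about 31,000 kits issued.

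A separate exploratory row in the same table names its endpoint as uptake by age band, ethnic group, LSOA, screening status and reason for past non-attendance. The measure counts women in each category, ending with "reason for previous non-attendance (survey data) as a % of all women who return a self-sample".

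**The concern.** The cost measure does not match the endpoint it serves, in four ways.

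- **Kits counted.** Adding kits sent to kits offered treats a declined offer as a kit consumed. Section 7.2.2 has the health professional record a kit ID only when the kit is accepted. The same section allows repeat offers to the same woman, so the excess would grow if offers rather than women were counted.
- **Costs counted.** Only the kit is priced. HPV testing, the pre-notification letter and postage are not named, and neither are follow-up tests.
- **Unit.** A cost per case is an amount of money per case. It cannot be a percentage of cases.
- **Missing ratio.** Cost per woman screened, the first quantity in the endpoint, has no formula.

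The kit count overstates the kit bill and the missing components understate the total, so a reader could not tell which way the published figure errs. Section 17 says the findings will be used to propose policy on self-sampling for non-attenders, where cost per woman screened and per case would naturally be quoted.

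In the exploratory row, the denominator of all returners gives the make-up of the returners, whereas the endpoint is called uptake.

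**Working it through.** **1. Reproduce the Protocol's kit numbers (sections 9.1.1, 9.1.2 and Trial Summary).**

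- Mailed: 106 practices × 9 months × 20 women = 19,080, stated as 19,000.
- Offered: 95,000 eligible × 0.60 consulting × 0.30 offered = 17,100, as stated.
- Accepted: 17,100 × 0.70 = 11,970, stated as about 12,000.
- Issued: 19,080 + 11,970 = 31,050, stated as 31,000.

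The stated figures reproduce.

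**2. Kits charged by the formula against kits issued.**

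| | Charged (sent or offered) | Issued (sent or accepted) | Ratio |
|---|---|---|---|
| Mail-out | 19,000 | 19,000 | 1.000 |
| Opportunistic | 17,100 | 12,000 | 1.425 |
| Total | 36,100 | 31,000 | 1.165 |

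The kit bill is 16.5% too high overall and 42.5% too high in the opportunistic pathway. The pathways are therefore not treated alike: all of the excess falls on the opportunistic one.

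**3. Effect on cost per CIN2+ case.** Set the kit cost to 1 and take 10,000 returns. The Protocol gives no planning value for CIN2+ detection, so three rates are assumed.

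| Assumed CIN2+ rate | Cases | 36,100 / cases | 31,000 / cases | Formula read literally as a % |
|---|---|---|---|---|
| 0.5% | 50 | 722 | 620 | 72,200 |
| 1% | 100 | 361 | 310 | 36,100 |
| 2% | 200 | 180.5 | 155 | 18,050 |

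The 16.5% excess does not depend on the assumed rate. Read literally, the percentage multiplies the ratio by 100.

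**4. The ratio with no formula.** Kit costs per returned sample would be 36,100 / 10,000 = 3.61 on kits sent or offered, and 31,000 / 10,000 = 3.10 on kits issued. Section 9.1's separate return estimates, 2,800 + 8,500 = 11,300, would give 3.19 and 2.74. The gap is again 16.5%.

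**5. The omitted testing cost.** About 10,000 tests against 31,000 kits is 10,000 / 31,000 = 0.32 tests per kit issued. The omission as a share of the kit bill is 0.32 × (test price / kit price). Neither price is in the Protocol, so this cannot be evaluated.

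**6. The exploratory uptake row (illustrative assumption).** Suppose two groups form 80% and 20% of the women offered kits, with true uptake of 25% and 50%. Returners are 0.80 × 0.25 = 0.20 and 0.20 × 0.50 = 0.10 of all those offered. The stated measure reports 0.20 / 0.30 = 66.7% and 0.10 / 0.30 = 33.3%, which reverses the order of the uptakes. As a profile of returners these shares are correct. As uptake they are not.

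**The case against.** **What can be said for the text.** Dividing by CIN2+ cases is the right denominator for cost per case. This is one secondary endpoint in a feasibility trial with no formal power calculation. The data for correct ratios are already to be collected: kit dispatch from the print company, acceptances from GP records, returns from the laboratory, and colposcopy from Cyres. Which costs to include depends partly on the costing perspective, which an analysis plan may set. All of this stands and limits the seriousness. It does not rescue the measure, because the Protocol does not leave the formula open: it writes one down, and no other section corrects it.

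**Stronger readings that the document does not support.**

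- *A reader might infer that the inequality objective would be answered wrongly because subgroup uptake has the wrong denominator.* That denominator belongs to an exploratory row whose objective is to describe women who respond. The inequality objective is a separate row, which compares returners with conventionally screened women and with overdue unscreened women. Section 9.2.2 also models uptake on ethnic group, LSOA and age.
- *A reader might object to the row reporting kits "accepted by health care professional type as a % of all kits offered (GP record data".* The same row reports kits offered by each type over the same denominator. Dividing one share by the other gives acceptance within type, so nothing is lost.
- *A reader might suspect differential classification because ethnicity comes from "British Census categories from GP records and self-report on survey".* The Protocol does not say that survey answers override GP coding, and section 10.4.4 provides GP-record data for all eligible women. How the two sources combine is analysis-plan detail.
- *A reader might put a large figure on the omitted tests.* Assuming a test costs one to three times a kit would give 32% to 97% of the kit bill at 10,000 tests, but that price ratio is not in the document.

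**Conclusion.** The concern holds for the cost-effectiveness measure. As written, it charges 36,100 kits where 31,000 are planned to be issued (+16.5% overall, +42.5% in the opportunistic pathway). It names no cost but the kit, states a cost ratio as a percentage, and leaves cost per woman screened undefined.

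The kit excess rests only on the Protocol's planning assumption that 70% of offers are accepted; the realised excess will depend on the actual decline rate. The omission of testing and mailing is clear from the text, but its size is unknown without unit costs, and so is the net direction of the error.

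In the exploratory row the fault is a mismatch between label and denominator, and it is minor. The primary endpoints and the inequality analysis are not affected. The correction is inexpensive and should be made before any cost result is reported.

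**What to change.** **Cost-effectiveness row, section 3.2.** Replace the measure with:

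- Numerator: (kits mailed + kits accepted, including repeat kits) × kit and mailing cost, plus samples tested × test cost. Either add follow-up costs or state the costing perspective that leaves them out.
- Two results, each an amount of money and not a percentage: the numerator divided by women with a valid self-sample result, and the numerator divided by women with confirmed CIN2+.

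State which unit cost is used for the kit, since section 8.1 has the swabs supplied free of charge for the trial.

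**Exploratory responder row.** For age, ethnic group, LSOA and screening status, either compute uptake as women returning a sample divided by women sent or offered a kit within the subgroup, in line with section 9.2.2, or relabel the measure as the profile of returners. Keep the share of returners for survey-reported reason for non-attendance. That item cannot have an uptake denominator: section 9.1.3 cites earlier survey response of "just under 1% for those who did not send back a kit".

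**Cost of the change.** Table wording, plus the work of obtaining unit costs for kits, mailing and tests. The volumes are already in the planned datasets.
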